### Follow-up evaluations

A follow-up 90 days after stroke will be conducted to verify functional capacity, muscle strength, mortality, and quality of life. The following will be assessed in each patient:Functional capacity according to the mRs and Timed Up and Go test scores.Muscle strength based on handgrip strength and lower limb strength according to NIHSS score and the 30-s chair stand test score.Patient perception of quality of life according to The European Quality of life Scale Five Dimension (EuroQol-5D) score.

### Procedures (template)

All patients with ischemic stroke confirmed by imaging examinations who meet the study inclusion criteria will be invited to participate. After signing the informed consent form, the patients will be randomized to the intervention or control groups. All patients will undergo clinical and neurological evaluations conducted by the medical team using the NIHSS score, which is used to determine treatment and predict prognosis; Bamford classification according to brain injury location; and the Alberta Stroke Program Early CT Score (ASPECTS), which verifies the extent of the injury [1, 21].

The template for the recommended schedule of enrollment, interventions, and assessments is presented in Fig. 2. To verify the occurrence of mortality, we will utilize death certificates from medical records.

**Fig. 2 Fig2:**
[figure not shown]
ICaRUS Stroke Trial template of recommended content for the schedule of screening, interventions, and assessments

### Sample size

We reviewed a study that analyzed the effects of creatine supplementation in 18 healthy older people, in which 10 patients were allocated to the creatine group and 8 to the control group. The authors observed an improvement in muscle strength, weight, and fat-free mass in the group that received supplementation [22]. In addition, a meta-analysis based on this previous study included approximately 600 patients from 60 studies, with an average of 10 patients in each arm per study [16]. Considering that this is a study on creatine supplementation in patients after stroke, we decided to include 50% more in the convenience sample, with a total of 15 patients in each group.

### Recruitment

Daily monitoring of admissions to the Stroke Unit of the Clinical Hospital of Botucatu Medical School, Brazil, will be carried out to refer individuals for screening and checking of inclusion criteria.

### Randomization and blinding

For all subjects, the screening visit and the enrollment visit were performed on the same day. Subjects were randomized 1:1 to the intervention or control groups. The randomization was performed using a cell phone application, which creates a random control and intervention sequence, and was performed in 10 out of 10 participants. No stratification factor was used.

To maintain the blindness of the study, randomization will be performed by a person uninvolved in data collection and data analysis. The participant, the professional responsible for administering the supplements, and the person responsible for conducting the protocol assessments will be blinded to the intervention. The professional in charge of the statistical analysis of the data will not be blinded to the intervention.

Breaking the blinding will be allowed if the participant has a serious adverse effect related to the supplementation, such as an allergic reaction. In this case, the principal investigator will be responsible for breaking the blinding and for informing the hospital’s medical staff about which supplement the participant was consuming.

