**Methods:**

Randomized, double-blind, unicenter, parallel-group trial including individuals with ischemic stroke in the acute phase. The duration of the trial for the individual subject will be approximately 90 days, and each subject will attend a maximum of three visits. Clinical, biochemical, anthropometric, body composition, muscle strength, functional capacity, degree of dependence, and quality of life assessments will be performed. Thirty participants will be divided into two groups: intervention (patients will intake one sachet containing 10g of creatine twice a day) and control (patients will intake one sachet containing 10g of placebo [maltodextrin] twice a day). Both groups will receive supplementation with powdered milk protein serum isolate to achieve the goal of 1.5g of protein/kg of body weight/day and daily physiotherapy according to the current rehabilitation guidelines for patients with stroke. Supplementation will be offered during the 7-day hospitalization. The primary outcomes will be functional capacity, strength, and changes in muscle mass after the intervention as assessed by the Modified Rankin Scale, Timed Up and Go test, handgrip strength, 30-s chair stand test, muscle ultrasonography, electrical bioimpedance, and identification of muscle degradation markers by D3-methylhistidine. Follow-up will be performed 90 days after stroke to verify functional capacity, muscle strength, mortality, and quality of life.

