## Methods

### Trial design

It will be a (randomization 1:1 to the intervention or control groups) double-blind (participants and researchers responsible for administering the supplement and carrying out the protocol assessments), unicenter, parallel-group trial including individuals with ischemic stroke in the acute phase to verify the superiority of the intervention compared to the control group. The duration of the trial for the individual subject will be approximately 90 days, and each subject will attend a maximum of three visits. The protocol was written according to the 2013 Standard Protocol Items: Recommendations for Interventional Trials (SPIRIT) guidelines. A flow diagram of the study is presented in Fig. 1.

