### Outcomes

The primary outcomes will be functional capacity, strength, and changes in muscle mass after the intervention. The evaluations will be conducted in the first 24 hours after stroke and on the 7^th^ day of hospitalization. The patients will be assessed for the following:Functional capacity according to the mRs and Timed Up and Go test scores.Muscle strength according to handgrip strength and lower limb strength according to the National Institutes of Health Stroke Scale (NIHSS) score.Muscle mass by muscle ultrasonography, electrical bioimpedance, and muscle degeneration markers by D3-methylhistidine.

A descriptive and comparative evaluation between groups in order to verify the inflammatory and potential serum biomarkers behavior during hospitalization will be performed with all participants randomized.

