### Statistical analysis

The Full Analysis Set (FAS) will comprise all randomized subjects who have received at least one dose of creatine. The subjects will contribute to the analysis as randomized. The FAS will be used for efficacy analysis instead of intention-to-treat analysis.

The Per-Protocol (PP) population will comprise all subjects in the FAS who do not have any major protocol deviations (including but not limited to violation of inclusion and exclusion criteria), and who have at least good compliance as reported in the eCRF and for whom the primary endpoint can be derived. The PP will be used for the analysis of the primary endpoint.

The Safety Analysis Set will comprise all subjects who have received at least one dose of creatine or placebo. The subjects will contribute to the analysis as actually treated. The Safety Analysis Set will be used for the evaluation of safety endpoints and the primary endpoint.

Missing values will be treated mathematically by multiple imputation.

All data will be analyzed using Stata SE version 15.0 (StataCorp LLC., College Station, TX, USA).

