#### Sensitivity analysis

The primary analysis will be repeated using the PP and safety analysis set. We will perform analysis using only patients with specific symptoms to each symptoms.

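### The statistician is unblinded without a stated reason while several analysis decisions are still open; coding the arms until they are locked would remove an avoidable source of bias

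*Protocol article*

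**What the plan says.** Under Randomization and blinding, the protocol article states: "The professional in charge of the statistical analysis of the data will not be blinded to the intervention". No reason follows. The same paragraph opens with a safeguard: "To maintain the blindness of the study, randomization will be performed by a person uninvolved in data collection and data analysis". Under Trial design, the trial is called "double-blind (participants and researchers responsible for administering the supplement and carrying out the protocol assessments"), so the statistician is not among those listed as blinded.

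The article leaves these decisions open:

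- **Primary measures.** Outcomes says: "The primary outcomes will be functional capacity, strength, and changes in muscle mass after the intervention". It then lists seven measures: the modified Rankin Scale (mRs), Timed Up and Go, handgrip, the NIHSS-based leg strength score, and three for muscle mass ("Muscle mass by muscle ultrasonography, electrical bioimpedance, and muscle degeneration markers by D3-methylhistidine"). The Abstract's Methods paragraph has "Modified Rankin Scale, Timed Up and Go test, handgrip strength, 30-s chair stand test, muscle ultrasonography, electrical bioimpedance" plus D3-methylhistidine. That is also seven, but with the chair stand test in place of the NIHSS leg score.
- **Muscle and side.** Baseline assessments has ultrasound on two muscles and both sides, and handgrip on both sides. None is designated as the one that counts.
- **PP membership.** Statistical analysis limits the set to patients without major deviations, given as an open-ended list, and "who have at least good compliance as reported in the eCRF". No threshold for good compliance is given.
- **Full analysis set (FAS).** The same section defines it by receipt of creatine. Read literally, that leaves out the control arm, so someone has to reinterpret it.
- **Subsets.** Sensitivity analysis adds: "We will perform analysis using only patients with specific symptoms to each symptoms". No symptom is named.

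**The concern.** An unblinded statistician is not an error in itself. If every measure, set and model were fixed beforehand, knowing the arms would matter little. Here the article combines open access to allocation with decisions that call for judgment. None of those decisions needs to know which arm received creatine, apart from the FAS wording, which looks like a slip.

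The risk is directional. Someone who knows the arms can, without intending to, settle a doubtful compliance case, a choice of side or a symptom subset in the way that favours the expected result. With 15 patients per arm, one or two such decisions can move an estimate noticeably. Keeping the randomiser out of data analysis also protects less than it could once the analyst is given the allocation anyway.

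**Working it through.** **Is there a stated need for the statistician to know the arms?** Data monitoring foresees no interim analysis, so no early comparison requires it. Unblinding after a serious adverse effect is assigned to the principal investigator, not the statistician. No other reason appears in the article.

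**How far could arm-aware exclusion move a PP result?** The protocol gives no figure for this, so the following is a worst-case illustration.

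Inputs: 15 per arm and a two-sided 5% level, from Sample size and Planned statistical methods. Assumptions: a normal outcome with SD 1, no true effect, a two-sample t-test, and exclusion of the lowest values in the creatine arm only.

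1. The expected lowest and second-lowest of 15 standard normal values are −1.736 and −1.248.
2. The 15 values sum to 0 in expectation. Removing the two lowest leaves a mean of (1.736 + 1.248) / 13 = 2.984 / 13 = **+0.23 SD**. Removing only the lowest leaves 1.736 / 14 = +0.12 SD.
3. Simulated two-sided type I error under no effect:

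| Exclusions from the creatine arm | Type I error |
|---|---|
| None | 5.0% |
| Two at random | 5.0% |
| The single lowest | 7.0–7.2% |
| The two lowest | 10.6–10.8% |

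The ranges are differences between simulation runs. In the last row, nearly all false positives favour creatine: about 10.0 percentage points, against 2.5 with no exclusions.

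The random-exclusion row shows that losing patients does no harm to type I error by itself. The inflation comes from exclusion that depends on both outcome and arm, and the dependence on arm is what coding removes.

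**What coding would not change.** Seven independent primary measures, each tested at 5%, give a chance of at least one false positive of 1 − 0.95^7 = 30.2%. The measures are probably correlated, so the true figure would be lower. This is multiplicity and is the same whether the arms are labelled A/B or by name. It is not counted as an effect of unblinding.

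**The case against.** The strongest reply is that the article openly discloses a design choice and contradicts nothing. That stands. A reader might infer that a trial labelled double-blind has broken its own label, but Trial design confines the term to participants, those giving the supplement and assessors.

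A reader might also infer that the statistician decides who is in the PP set. The article does not say who does. Compliance is taken from the eCRF, and the people giving the supplement and making the assessments are blinded. So the point is that nothing in the article keeps this decision apart from knowledge of the arms, not that the analyst is known to make it.

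It is also tempting to multiply measures by tests by analysis sets and present the product as a count of available primary p-values. The text does not support that. The t-test or Mann-Whitney choice is stated for characteristics between the groups, while muscle mass, strength and biomarkers go to mixed regression models. The FAS is named for efficacy, and the PP and safety sets appear under Sensitivity analysis as repeats announced in advance. Such a count would in any case mostly measure multiplicity.

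Finally, an analysis plan that is not shown may settle some of these matters. The imputation model and the rule for choosing a test belong there, and their absence is not held against the article. But such a plan would not remove the sentence on the unblinded statistician, or the two differing lists of primary measures.

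**Conclusion.** The point holds as a modest, practical design weakness that should be changed. The article fixes an unblinded statistician without a reason, leaves judgments open that could be settled without knowing the arms, and already has an independent person performing the randomisation.

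The figures of +0.23 SD and about 10.6–10.8% are worst cases for the PP analysis alone. They assume that exclusions fall entirely on the two worst outcomes and only in the creatine arm. A reader might take them as the trial's type I error or as a prediction of misuse. They are neither: the FAS analysis would still stand beside the PP result, and exclusions unrelated to outcome leave the error at 5.0%. The conclusion rests on the explicit sentence and the open decisions, not on the simulated size.

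**What to change.** Replace the sentence on the statistician with:

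> The statistician will receive data with arms coded A/B; primary measures, analysis-set membership, protocol deviations, symptom subsets and analysis programs will be finalised and dated on coded data, and the person who performed the randomisation will release the code only after database lock and sign-off.

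The FAS definition has to be restated in terms that do not depend on which product was taken, because as written it cannot be applied to coded data.

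The cost is recoding one variable and keeping a dated sign-off. Sample size and significance level do not change. The trial is described as ongoing, so the change can be made for any data not yet analysed; if the statistician has already seen allocation, the report should say so. Multiplicity across the primary measures, and whether the symptom subsets should be kept, are separate matters that this change does not resolve.

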### Data collection, management, and analysis

All collected data will be de-identified and stored in a safe place to protect the confidentiality of each participant. After 5 years from the end of the research, the data will be destroyed. Subjects in both groups will be evaluated in the first 24 h after the stroke, after 7-day hospitalization, and 90 days after stroke. All individuals who participate in the study will be instructed to complete the protocol during the 7 days of hospitalization in the stroke unit. The research team will carry out daily visits during the 7 days of hospitalization to guarantee the participant’s permanence in the study. After hospital discharge, the team will contact the participant by telephone to ensure the follow-up visit 90 days after the stroke. In case of loss of contact, the researchers will count on the social service of the hospital to carry out an active search for the participant.

All data will be double-checked by 2 team researchers to promote data quality (e.g., double data entry; range checks for data values).

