### Participants and eligibility criteria

Men and women aged 60 years and older who were diagnosed with ischemic stroke without previous disability (Modified Rankin Scale [mRs] – [mRs≤2]) and agree to sign the informed consent form will be recruited within 24 h of stroke.

Patients with any of the following will not be included: hemodynamic instability, mechanical ventilation, pacemakers and metallic prostheses, previous kidney disease, creatinine clearance ≤30 ml/min/1.73 m^2^, history of disabsorptive gastrointestinal surgery, parenteral nutrition, allergies or intolerance to any component of the study products, and patients who decline to participate.

The study will be conducted at the Stroke Unit of the Clinical Hospital of Botucatu Medical School, Brazil, and the follow-up visits at the Neurovascular Disease Outpatient Clinic of the same institution.

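### As described, the day-90 mRs and EuroQol-5D depend on attending the outpatient clinic, so survivors too disabled to travel risk having no value on the outcomes that measure disability

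*Protocol article*

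**What the plan says.** The section on participants and eligibility fixes the place of follow-up: "the follow-up visits at the Neurovascular Disease Outpatient Clinic of the same institution". The section on follow-up evaluations sets out what is done then: "A follow-up 90 days after stroke will be conducted to verify functional capacity, muscle strength, mortality, and quality of life". Among the measures listed there are "Functional capacity according to the mRs and Timed Up and Go test scores" and "Patient perception of quality of life according to The European Quality of life Scale Five Dimension (EuroQol-5D) score", along with handgrip strength, the NIHSS leg item and the 30-s chair stand test.

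The data collection section describes how participants are retained after discharge: "After hospital discharge, the team will contact the participant by telephone to ensure the follow-up visit 90 days after the stroke". The back-up is a search by the hospital's social service, used when contact has been lost. It names no other way of obtaining day-90 data. For gaps in the data, the statistical analysis section says: "Missing values will be treated mathematically by multiple imputation".

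Three other statements limit the point. The primary outcomes are measured in hospital: "The evaluations will be conducted in the first 24 hours after stroke and on the 7^th^ day of hospitalization". The procedures section takes mortality from death certificates in the medical records. The functional capacity section scores death as mRs 6.

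**The concern.** The mRs is a disability rating and the EuroQol-5D a questionnaire. Neither, as the article describes them, includes a physical test. Both are nevertheless obtained at a clinic visit, and that visit is hardest for the patients who would score worst. Participants are at least 60 years old and have had a stroke, and the article's own background names reduced mobility and functional dependence among its consequences. Severe disability is thus a plausible reason for a missing day-90 value.

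Both safeguards miss this case. The call is there to bring the patient to the clinic, and the search is there to find a patient who cannot be reached. A patient who is reached but cannot travel falls between them.

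At stake are two of the stated day-90 aims, functional capacity and quality of life. If severely disabled survivors are under-represented, both arms look less disabled than they are and a true difference in severe disability is likely to look smaller. With 15 patients per arm, a few absences are enough to matter.

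**Working it through.** **The plan's own figures.** The article gives no non-attendance rate, no expected mRs distribution and no dropout allowance. Its only relevant figure is the sample size: 10 per arm in earlier studies, plus 50%, gives 10 × 1.5 = 15 per arm and 2 × 15 = 30 in total. This reproduces. Everything below rests on assumed rates.

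**Which day-90 data depend on the visit**

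| Item | Needs the clinic visit as described? | Needs physical attendance in principle? |
|---|---|---|
| Death (and mRs 6) | No, death certificates | No |
| mRs 0-5 | Yes | No |
| EuroQol-5D | Yes | No |
| Timed Up and Go, handgrip, NIHSS leg item, chair stand | Yes | Yes |

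**Complete-case illustration among survivors.** Let p be the true proportion with mRs 4-5 and m the share of these who do not attend, with everyone else attending. The proportion seen among attenders is p(1 − m)/(1 − pm). Assume p = 0.30 in controls and 0.15 on creatine, a true difference of 15 points.

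| m | Control | Creatine | Observed difference |
|---|---|---|---|
| 0.25 | 0.225/0.925 = 24.3% | 0.1125/0.9625 = 11.7% | 12.6 points |
| 0.50 | 0.15/0.85 = 17.6% | 0.075/0.925 = 8.1% | 9.5 points |
| 0.75 | 0.075/0.775 = 9.7% | 0.0375/0.8875 = 4.2% | 5.5 points |

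**Whole-patient check.** Suppose 6 of 15 controls and 2 of 15 on creatine have mRs 4-5 (40.0% and 13.3%, difference 26.7 points). If half of them are absent, the attenders show 3/12 = 25.0% and 1/14 = 7.1%, a difference of 17.9 points with 4 patients lost. If both arms have 4 of 15 (26.7%), each shows 2/13 = 15.4%. The difference stays at zero, but both arms look less disabled.

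**How many patients.** In the 50% row, taking all 15 per arm as survivors, the expected number absent is 15 × 0.30 × 0.5 = 2.25 controls and 15 × 0.15 × 0.5 = 1.1 on creatine, about 3 in all.

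**What imputation can and cannot do.** Each absent patient has an mRs and an NIHSS leg score from the first 24 h and from day 7. A model using these can separate patients who were severely affected in hospital from those who were not, so it should recover part of the loss. Under the usual missing-at-random assumption, it would still treat an absent patient like an attender with the same in-hospital scores. If the absent patient became more disabled after discharge and stayed away for that reason, the imputed value would be too favourable. The article does not state the imputation model, so the residual bias cannot be calculated.

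**The case against.** The strongest objection is that this is a condensed article. What happens when a reached patient cannot travel is an operational detail that the full protocol may settle, and the schedule figure is not visible. That caution stands: the article does not prove that no fallback exists. But it is not simply silent. It names the place of the visit, the purpose of the call and the trigger for the search, and that stated procedure can be improved.

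A reader might go further and infer that patients too disabled to travel are dropped. The article does not say so. It has no rule excluding non-attenders and gives no rate, and it sends missing values to multiple imputation. The risk of a missing value is an inference from the procedure.

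A reader might also take the 50% row to mean that over a third of any effect would be lost (5.5 of 15 points). That is not supported either. The row describes attenders only, on assumed rates, before imputation and leaving deaths out, although deaths need no visit and can be scored mRs 6.

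The practical weight is also limited. On the central assumptions about 3 patients are involved. The 5.5-point shrinkage compares with a standard error for the difference of √(0.30 × 0.70/15 + 0.15 × 0.85/15) = 0.15, or 15 points. This argues for a modest priority, not against a cheap correction.

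Two objections to the remedy hold. The article does not date the telephone contact, so it cannot be assumed to fall at day 90. And because the EuroQol-5D is defined there as the patient's own perception, caregiver answers would change the outcome in just the most disabled patients.

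**Conclusion.** The point holds as a risk built into the described procedure. Day-90 mRs in survivors and EuroQol-5D depend on clinic attendance, no stated route covers a patient who is reached but cannot travel, and the resulting gaps would plausibly depend on disability. Multiple imputation may correct this only in part.

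Its reach is limited to the day-90 follow-up: mortality and the day-7 primary outcomes are unaffected. Its size is unknown. The 12.6, 9.5 and 5.5 points against a true 15 show how attenders alone would mislead. They assume mRs 4-5 in 30% and 15% of patients, the same share absent in both arms, and full attendance by everyone else. It is worth acting on because the values can be collected for little effort, which is better than relying on an unspecified imputation model to supply them.

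**What to change.** Add to the follow-up evaluations and data collection sections that, when a participant cannot attend at day 90:

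- the blinded assessor obtains the mRs by telephone at day 90, from the caregiver if the patient cannot answer;
- the EuroQol-5D is obtained by telephone from the patient;
- the mode of collection and the respondent are recorded.

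Analyse the mRs from either mode. Keep any caregiver-reported EuroQol-5D separate, for a sensitivity analysis only. Clinic attendance stays required for handgrip, Timed Up and Go, the NIHSS leg item and the chair stand test. If the full protocol already provides such a route, stating it in these sections is enough.

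The cost is one short day-90 call for each non-attender, made by staff the trial already has, and an ethics amendment. Recruitment has run since March 2019, so the amendment can help only participants who have not yet reached day 90, and the mode of collection will differ over the course of the trial. Telephone ratings are somewhat less precise than clinic ratings, which is why the mode should be recorded.
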